### Data analysis

All analysis will be performed according to group using an intention-to-treat method. The primary outcomes of combined hospitalizations and ED visits will be analyzed using a time-to-event, Cox proportional analysis. Adjustment will be made to the time-to-event analysis only if there are clear differences between the randomized groups. As a secondary method of analysis, the total number of ED visits and hospitalizations will be compared using a t-test. Initial descriptive data will be presented with means and standard deviations for parametric data. Non-parametric data will be presented with modes and 25 to 75 interquartile ranges.

Secondary data analysis will involve comparisons between the intervention group and the usual care group, with these dependent variables: SF-12 scores and sub scores, PHQ-9 scores, Kokmen Short Test of Mental Status scores, Katz Index of Independence in Activities of Daily Living scores, and Likert Scale scores for attitudes toward health and compliance (Table 4). All categorical variables will be analyzed using a t-test where appropriate, and proportional variables will be analyzed using chi square analysis for secondary outcomes. All tests for significance will use an alpha *p*-value of 0.05. Adjustments for multiple comparisons will be used for secondary analysis. All tests will assume a two-sided *p*-value.

**Table 4 T4:** Statistical analysis for secondary outcomes

Instrument/measure	Variable type	Test	Significance
**Kokmen Short Test of Mental Status**	Continuous score	t-test	Alpha 0.05

**SF-12**	Proportional for items or continuous	Fisher's exact test or t-test	Alpha 0.05

**Likert scale scores for attitudes and behavior**	Continuous	t-test	Alpha 0.05

**PHQ-9**	Continuous	t-test	Alpha 0.05

**Katz Index of Independence in Activities of Daily Living**	Continuous	t-test	Alpha 0.05

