## Methods/Design

### Study design

This multi-site, randomized controlled trial of home telemonitoring or usual care will take place in the four sites of the outpatient practice of Mayo Clinic's Division of Primary Care Internal Medicine (PCIM) in the Department of Family Medicine (FM) in Rochester, Minn. and nearby Kasson, Minn. The Mayo Elder Risk Assessment (ERA) Index will be used to randomly assign 200 high-risk patients to home telemonitoring or usual care (100 patients per intervention). Patients will be followed for 1 year after enrollment. Patients in the Rochester practice will be block-randomized as a single entity, and the patients in the Kasson practice will be block-randomized as a second entity. Subjects and providers will not be blinded to the allocation of the intervention, but analysis will be blinded to the allocation type.

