### Demographic and practice information

Most residents of Olmsted County who are age 60 or older are female and white (>90%)[4]. While county residents are largely Northern European, the ERA index places this ethnicity as a high-risk population; thus, the potential sample may slightly over represent underserved minorities as a high-risk group.

The PCIM and FM have a combined population of about 21, 000 patients in this age group. The selection criteria of a score of 16 or greater on the ERA places these individuals in the upper decile of risk for hospitalizations, ED visits, nursing home placement, and death. The ERA is an electronically derived index number provided to all patients in the in PCIM and FM via the GDMS (Table 1).

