### Sample size

Using an alpha value of 0.05 and a power of 80%, the power calculations were derived from an estimated 76% event rate of hospitalizations and ED visits in 2 years in the high-risk group. Using a time-to-event approach with a 25% reduction when the sample size in each group is 352, with a total number of events required, E, of 463, a 0.050 level two-sided log-rank test for equality of survival curves will have 80% power to detect the difference between a Group 1 proportion π_1 _at time t of 0.380 and a Group 2 proportion π_2 _at time t of 0.285 (a constant hazard ratio of 0.771); this assumes no dropouts before time t. Using 100 patients in each group with a yearly hospitalization/ED rate of 38.2%, we will be able to detect a 36.1% decrease in combined outcomes. Table 3 below reflects the changes with different size groups.

**Table 3 T3:** Sample sizes for hospitalizations and emergency department visits

Sample size	% hospitalized in intervention	% with ED/hospitalization in intervention
100	27.1 (42.5% drop)	38.2 (36.1% drop)

150	30.7 (34.8% drop)	42.1 (28.6% drop)

200	32.9 (30.1% drop)	44.4 (24.6% drop)

250	34.4 (27.0% drop)	46.0 (21.9% drop)

300	35.5 (24.6% drop)	47.2 (19.9% drop)

350	36.4 (22.7% drop)	48.1 (18.3% drop)

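### The primary Cox model is not fixed in advance: covariate adjustment depends on an undefined judgement of imbalance, and the text gives no place to the Rochester and Kasson randomization strata

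*Protocol article*

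**What the plan says.** The Data analysis section states that the combined primary outcome "will be analyzed using a time-to-event, Cox proportional analysis". It then adds: "Adjustment will be made to the time-to-event analysis only if there are clear differences between the randomized groups". It does not say which variables are compared, how large a difference must be, who decides, or which covariates would enter. I read the sentence as referring to baseline characteristics, although it does not say so.

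Under Study design: "Patients in the Rochester practice will be block-randomized as a single entity, and the patients in the Kasson practice will be block-randomized" as a second unit. The same section says "analysis will be blinded to the allocation type". The Data analysis section does not mention practice.

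Under Demographic and practice information: "The ERA is an electronically derived index number provided to all patients". That section ties the entry threshold to the top tenth of risk for hospitalization and ED visits, among other outcomes. A baseline risk score for the primary outcome is therefore on file for every participant.

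The Sample size section plans on an unadjusted comparison: "a 0.050 level two-sided log-rank test for equality of survival curves will have 80% power".

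**The concern.** Under proper randomization, baseline differences arise by chance. Their size does not show whether a variable predicts outcome, so it is a poor guide to what belongs in the model. A rule driven by imbalance has two possible costs.

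- **Error control.** If the trigger is undefined, an adjusted and an unadjusted result may both be available, and either can be defended as the primary one.
- **Power.** In most trials the rule ends with no adjustment. Any gain from a prognostic covariate is then forgone, although that gain does not depend on imbalance.

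Separately, the conditional wording provides no standing place for the randomization strata, so the analysis as written does not follow the design.

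**Working it through.** **The plan's own figure.** Reading 0.380 and 0.285 as event-free proportions, HR = ln(0.380)/ln(0.285) = 0.771, as stated. With (1.960 + 0.842)² = 7.85:

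- Freedman: 7.85 × ((1 + 0.771)/(1 − 0.771))² ≈ 469 events.
- Schoenfeld: 4 × 7.85/(ln 0.771)² ≈ 464 events (stated: 463).
- Per group: 469/(0.620 + 0.715) = 351.3, so 352, as stated.

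The figures reproduce, and they describe a crude log-rank comparison with no covariates.

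**Inputs for the check.** 100 per group, 1 year, no dropout and two-sided 0.05 come from the article. Table 3 gives 38.2% in the intervention arm for 100 per group. The control rate follows as 38.2/(1 − 0.361) = 59.8% from that row, or 58.9% from other rows, for example 44.4/(1 − 0.246). Hence HR = ln(0.618)/ln(0.402) = 0.528, or ln(0.618)/ln(0.411) = 0.541. The section's text calls 38.2% a yearly rate instead; I followed Table 3. Assumed: the covariate's log HR per SD (0 to 0.8), site effects, and blocks of 4 within two sites. Each setting has 3,000 simulated trials. The Monte Carlo error of one power figure is about √(0.85 × 0.15/3000) = 0.65 points, and all models were fitted to the same trials.

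**How often chance alone shows a difference.** With five independent covariates each tested at 0.05, 1 − 0.95⁵ = 22.6% of trials show at least one (simulated: 21.5% to 23.6%).

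**Type I error.**

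- Adjustment for one covariate, triggered at p < 0.05: 4.2% to 4.9%.
- Five covariates, unadjusted model: 4.3% to 5.5%.
- Five covariates, adjusted model: 4.9% to 6.0%.
- Free choice of the more significant of these two models: 6.0% to 7.5%. This is 1.0 to 3.2 points above the unadjusted model in the same trials (5.97 − 4.83 = 1.1 at no association; 7.47 − 4.27 = 3.2 at 0.8).

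**Power, one covariate, HR 0.528.**

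| log HR per SD | Unadjusted | Site-stratified | Adjusted only on imbalance (p < 0.05) | Always adjusted |
|---|---|---|---|---|
| 0 | 88.1% | 88.2% | 88.0% | 88.4% |
| 0.3 | 86.8% | 86.6% | 86.9% | 88.7% |
| 0.5 | 82.9% | 83.2% | 83.7% | 88.0% |
| 0.8 | 75.8% | 75.9% | 77.0% | 88.9% |

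With HR 0.541, five covariates and 10% of patients at the smaller site, unadjusted against always adjusted gives 83.5% against 83.1% at 0, 83.2% against 84.5% at 0.3, 79.5% against 85.3% at 0.5, and 71.3% against 84.5% at 0.8.

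Always adjusting therefore gains about 0 points at no association, 1 to 2 at 0.3, 5 to 6 at 0.5 and 13 at 0.8. The triggered rule recovers about 1 point at most: 83.7 − 82.9 = 0.8 at 0.5, against 88.0 − 82.9 = 5.1.

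**Strata.** Across all settings, stratifying by site changed power by at most 0.3 points and the null rejection rate by at most 0.2 points.

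**The case against.** **The article is condensed, and an SAP may define the trigger.** This stands in part. A defined trigger would remove the error-control concern. It would leave the power point, because the article fixes the form of the rule: adjustment only on imbalance. An SAP with an unconditional adjusted model would contradict it. On the strata, the sentence can be read as concerning covariates only. Silence about practice would not be a finding by itself; it matters here because this sentence needs rewriting anyway.

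**Analysis is blinded to allocation.** This limits steering toward telemonitoring. It does not fix the model, since differences between coded groups remain visible. The 6.0% to 7.5% figure counts significance in either direction, which coded groups also reveal. It does, however, require someone to choose the more favourable model, and nothing in the article says that this is intended.

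**The power gain is assumed.** This stands. No ERA–outcome association is given, and enrolling the top decile narrows the score. Some range remains: the Table 1 items without race points reach 7 + 11 + 2 + 3 + 2 + 5 = 30, against an entry threshold of about 16.

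**The trial was sized on crude proportions, so an unadjusted model loses nothing it was sized for.** This stands. The simulation holds the conditional hazard ratio fixed, so unadjusted power falls by construction as the covariate strengthens. The differences between models within a row carry the argument, not the levels. A gain is forgone; planned power is not lost.

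**Fixing the unadjusted model would cure the data dependence equally well.** This also stands.

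**Conclusion.** The point holds in a limited form. The primary model depends on an undefined judgement and should be fixed in advance. This conclusion rests on the text and needs no simulation. Its size is moderate: no inflation under a fixed trigger, about 6.0% to 7.5% if the better of two models could be reported, and a forgone power gain of roughly 0 to 6 points for log hazard ratios from 0 to 0.5 per SD, with the low end likelier. The 13 points at 0.8 need a strength that is hard to expect in so selected a group.

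A reader might infer more, and the documents do not support it:

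- **That ignoring the practice strata wastes power.** The difference is at most 0.3 points; the reason to stratify is consistency with the randomization.
- **That the rule in itself inflates type I error.** With a fixed trigger it does not.
- **That the unadjusted hazard ratio is biased toward 1.** The shift is non-collapsibility of the Cox model: the crude and conditional hazard ratios are different quantities.

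The change is worth making, but the defect does not endanger the trial.

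**What to change.** Replace the conditional sentence in the Data analysis section with:

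> The primary analysis is a Cox model stratified by randomization stratum (Rochester, Kasson) and adjusted for continuous baseline ERA score, whatever the observed balance; the unadjusted model is a sensitivity analysis.

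Add that the reported hazard ratio is conditional on ERA. If the sponsor prefers no covariate, naming the unadjusted model stratified by practice as primary also removes the data dependence, but forgoes any gain from ERA.

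The cost is one sentence plus that note; practice and ERA score are already held for every patient. The small downside is that the adjusted hazard ratio is not the same quantity as the crude comparison used for the sample size. Keeping the unadjusted result as a sensitivity analysis preserves that link.

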The instruments used in this study measure quality of life, mood, functional status, activities of daily living, caregiver burden, and self-reported outcomes of hospitalization and ED visits. The SF-12, the short form of the SF-36, which measures quality of life and psychosocial factors[7], will determine if the quality of life has changed due to the intervention. The PHQ-9 is a validated instrument that measures depression using Diagnostic and Statistical Manual (DSM) 4 criteria for depression[5] and a scoring mechanism that can measure depressive symptoms over time. The Kokmen Short Test of Mental Status screens for cognitive decline using a 38-point screening instrument[6]. The functional measures include grip strength with tonometry, which can directly measure a person's strength in the upper extremities[8]. Both upper extremities will be tested and the best result used as the primary measure. The timed up-and-go test is a validated instrument that measures the ability to rise from a chair, turn, and return to the chair[9]. Lastly, gait speed is measured in meters per second. The patient is told to walk as quickly as possible for 6 meters. Standards for gait speed are established for older adults[10]. The Barthel Index is a self-reported questionnaire that evaluates activities of daily living for the subject[11]. The Caregiver Quality of Life Scale is used as the standard instrument for measuring caregiver stress and feelings. Outcomes include hospital admissions and visits to the ED within the past 3 months. The healthcare providers are surveyed once in the pre-stages of the study and once after completion. Providers are asked these questions:

• How confident are you in the home monitoring of your sickest patient?

• Do you feel that our practice has a good system of maintaining the functional status and health of our patients?

• How confident are you that a home-based system that allows monitoring of vital signs and symptoms will help in patient care?

• Would you be willing to recommend a home-based telemonitoring system that allows videoconferencing?

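### The descriptive rule pairs the mode with an interquartile range for skewed data, where the median belongs (minor, reporting only)

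*Protocol article*

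**What the plan says.** The Data analysis section gives one rule for each type of descriptive data. For the first type: "Initial descriptive data will be presented with means and standard deviations for parametric data". The next sentence covers the rest: "Non-parametric data will be presented with modes and 25 to 75 interquartile ranges". The article does not name the median anywhere.

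Comparisons between groups are specified separately in the same section. The combined outcome "will be analyzed using a time-to-event, Cox proportional analysis". As a secondary method, "the total number of ED visits and hospitalizations will be compared using a t-test". Secondary scores are compared by t-test, and proportions by chi-square or Fisher's exact test (Table 4). The section also allows the Cox model to be adjusted when the randomised groups clearly differ, without saying how that is judged.

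The trial collects variables that are likely to be skewed or discrete. The Assessments section lists timed up-and-go, walking speed ("gait speed is measured in meters per second"), PHQ-9, and admissions and ED visits in the past 3 months. The Background adds hospital bed days and costs. The Study design section sets "100 patients per intervention" and 1 year of follow-up.

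**The concern.** An interquartile range describes the middle half of the data, and the median is the value it surrounds. The mode is the most frequent recorded value. It has no fixed relation to the quartiles and need not lie between them.

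Two kinds of variable in this trial show the difficulty. For a time or speed measured finely on about 100 people, few values repeat, so the mode is whichever value happens to tie most often, and there may be several. For a count with a low event rate, the mode is often 0 and says little about how many events occurred.

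A reader of the resulting table would get a central value that is unstable, may not be unique, or conflicts with its own range. If such tables are used to decide whether the groups differ clearly enough to adjust the Cox model, a noisy mode could suggest an imbalance that is not there or miss one that is. That use is possible, but the protocol does not state it.

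**Working it through.** The plan gives no figure for this point, so there is none to reproduce. The check asks how the mode behaves for the kinds of data collected.

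**Inputs from the protocol.** There are 100 patients per arm and 1 year of follow-up. In Table 3 at 100 per group, 38.2% of the intervention arm have an ED visit or admission (a 36.1% drop) and 27.1% are hospitalised (a 42.5% drop). The implied control rates are 38.2/(1 − 0.361) = 59.8% and 27.1/(1 − 0.425) = 47.1%. The Sample size text also calls 38.2% the yearly rate. On that reading a 36.1% drop gives 38.2 × (1 − 0.361) = 24.4%.

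**Inputs assumed.** The protocol gives no distribution for counts or times. Counts are taken as Poisson, or negative binomial with dispersion k = 2, 1 or 0.5. Times are taken as lognormal with median 14 s and log-SD 0.3 to 0.5, recorded to 0.01, 0.1 or 1 s.

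**1. Timed measures, n = 100, ties broken at random.**

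| Log-SD | Recorded to | SD of mode (s) | SD of median (s) | Mode tied | Mode outside IQR |
|---|---|---|---|---|---|
| 0.3 | 0.01 s | 3.07 | 0.53 | 82% | 34% |
| 0.3 | 1 s | 1.69 | 0.60 | 18% | 5% |
| 0.4 | 0.1 s | 3.09 | 0.70 | 58% | 26% |
| 0.5 | 0.01 s | 5.56 | 0.87 | 71% | 38% |
| 0.5 | 1 s | 2.75 | 0.91 | 23% | 16% |

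The ratio of the two SDs runs from 1.69/0.60 = 2.8 to 5.56/0.87 = 6.4, so about 3 to 6. With gamma-distributed times instead, the ratio was about 3 to 5 and the mode lay outside its own interquartile range in 17% to 54% of samples.

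**2. Counts.** Set P(0) = 1 − p, where p is the proportion with any event. Under Poisson the mean is −ln(1 − p). Under the negative binomial with k = 1 it is p/(1 − p).

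- Control at 59.8%: −ln(0.402) = 0.91, or 0.598/0.402 = 1.49.
- Intervention at 38.2%: −ln(0.618) = 0.48, or 0.382/0.618 = 0.62.

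The means differ clearly, yet the population mode is 0 in both arms under all four count models. The same holds at 47.1% vs 27.1% and at 38.2% vs 24.4%. In samples of 100 at 59.8%, the mode is 0 in 69% of trials under Poisson, rising to 100% at k = 0.5.

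**3. Does the median repair the counts?** Only in part. At 59.8% vs 38.2% the population medians are 1 and 0. At 47.1% vs 27.1% and at 38.2% vs 24.4% they are 0 and 0. Counts therefore also need a mean or a frequency distribution.

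**4. Does any inference depend on the rule?** The planned methods are Cox, t-test, chi-square and Fisher's exact test. None takes the mode as input.

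**The case against.** The strongest case against is that this is a slip of one word in a sentence about presentation. It follows a sentence about initial descriptive data, so its natural scope is baseline tables, and at baseline randomised arms have no treatment effect to conceal. Outcomes are compared by other methods, and the t-test on total events already compares means. The interquartile range printed beside the mode still carries information. Timed up-and-go and gait speed are not among the dependent variables in the Data analysis section or Table 4.

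Most of this stands, and it sets the size of the point. It does not make the sentence right: the mode is what the rule prescribes, and nothing else in the article corrects it.

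A reader might infer something stronger, that the plan would hide a real difference in event counts between the arms. The documents do not support that. The rule is not tied to the outcome comparison, and the size of any masking depends on an overdispersion that the protocol does not give. For example, take assumed mean counts of 1.3 and 0.83 with 100 per arm. The arms share a mode in 28% of simulated trials under Poisson, 55% at a frailty variance of 0.25, 84% at 0.5, and 99% only at 1. Across that span the two interquartile ranges still differ in about 86% to 94% of trials. Under Poisson the arms share a median in about 88% of trials, so there the median would mask the difference more often than the mode.

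**Conclusion.** The point holds as a minor error in descriptive reporting. The mode is the wrong companion to an interquartile range. For timed measures it is about 3 to 6 times as variable as the median at n = 100, is often tied, and can fall outside the reported range. For low counts it is often 0 whatever the mean.

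The direction of these results follows from what a mode is. The sizes rest on the assumed distributions and recording precision. The count results also rest on one-year event rates: if the protocol's two-year rate of 76% were used, the control mode could be 1, but follow-up is 1 year.

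No test, p-value, power or sample size changes. The only route to the analysis is indirect, if descriptive tables inform the decision to adjust the Cox model.

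**What to change.** In the Data analysis section, replace *modes* with *medians*, so that non-normal data are given as medians with 25th and 75th percentiles. For count variables (admissions, ED visits, bed days), add a mean or a frequency distribution, because the median can also be the same in both arms. The cost is one word and one extra row per count variable. Design, sample size and primary analysis stay as they are.

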## Discussion

Appropriate, efficient, and cost-effective care for older adults remains an important objective for both patients and providers in healthcare. It is predicted that the number of adults older than age 65 will double in the next 20 years[4]. These older adults are at higher risk for accidents and geriatric conditions such as urinary incontinence [12]. The large post-World War II cohort will require changes in how healthcare is delivered as a result of both increased numbers and required intensity of care. The utilization of efficient systems may help to mitigate some of the potential shortages of staff and resources. Telemonitoring has emerged as one possible solution to help efficiently care for older adults[13]. The potential advantages of telemonitoring are many; however, one must look at the potential costs involved with such a system.

The earliest methods of home monitoring were limited to periodic nurse telephone support, with or without other limited forms of data transmission such as cardiac rhythm monitoring. Telephone-based care has been used successfully, particularly in congestive heart failure (CHF), with a demonstrated 50% reduction in hospital readmissions through the use of nurse telephone support with remote cardiac rhythm monitoring[14]. However, the clinical desire to provide more frequent and detailed monitoring of expanded physiologic parameters and to have a remote "face-to-face" interaction with the patient has lead to the development of more sophisticated telemonitoring equipment. This equipment provides direct visual and audio communication through video monitoring and expands the ability to frequently assess patient status via capabilities (e.g., oximetry, spirometry, direct vital sign measurement, remote auscultation, blood glucose measurement). It can be monitored in a synchronous fashion to facilitate early intervention. One might easily imagine this type of technology to have the greatest impact potential for older adults who may be challenged to collect their own physiologic data and communicate well solely over the telephone.

Telemonitoring using updated equipment has been quite successful for chronic disease management. The initial use of telemonitoring targeted patients who live long distances from medical or specialty care[15]. Increasingly, telemonitoring has sought to help individuals with chronic illnesses (e.g., CHF, chronic obstructive pulmonary disease [COPD], diabetes) that require daily or frequent monitoring. The goal of telemonitoring is to identify and treat symptoms, functional decline, and other key changes in medical status before the patient requires acute care in an ED or hospital or long-term care in a skilled nursing facility. The results of many demonstration projects and pilot studies evaluating the effectiveness of telemonitoring have been favorable; however, the projects have been often limited to a single disease model. Diabetes has been widely studied in randomized controlled trials[16-18]. In the diabetic population, using a meta-analysis, on aggregate, the patients favorably endorsed home telemonitoring and had lower hospital readmissions and improved hemoglobin A1c levels[3]. In the CHF studies, all-cause mortality dropped by 40% and hospitalizations by 20%[3]. Some of the CHF studies did not demonstrate a decrease in ED visits compared with usual care[19].

Patients with mixed chronic diseases remain the most understudied group, yet many older adults have more than one chronic illness[20]. In a randomized controlled trial of 53 patients with CHF, COPD, or a chronic wound, fewer patients were re-hospitalized in the telemonitoring group, which used a device capable of videoconferencing and physiologic monitoring of vital signs, spirometry, and pulse oximetry[21]. In a similar study of 104 patients with CHF, COPD, and/or diabetes, Noel[22] demonstrated reduced bed days and ED visits when patients at home used a device capable of measuring vital signs, blood glucose levels, three-lead electrocardiography, pulse oximetry, auscultation of heart and lungs, and pain assessment. However, cost analysis was limited to a previous 6-month comparison, making interpretation difficult. Videoconferencing was not available for this study. In a recent review for the Canadian government, this study was the only publication on elderly patients with mixed chronic disease given the quality score of B (good), with the remainder deemed to have significant shortcomings[3].

The primary concern for many healthcare organizations undertaking telemonitoring is the cost justification for the clinical and capital investment. While the cost benefits of reduced utilization and functional decline are self-evident, the costs of telemonitoring have not been well-analyzed to date. In an example analysis of a single published work, the estimated annual cost for patients in the telemonitoring group was $14,678, compared with $10,161 for the usual care[3]. However, remaining methodologic issues suggested lack of comprehensive cost accounting and validated staffing protocols. Moreover, the quality of the economic evaluations to date have been deemed poor, and the report called for more studies of higher methodologic quality to include more diverse patient populations with CHF, diabetes, and COPD to increase external validity[3].

The proposed study will address the need for more rigorous study of the role of home telemonitoring in elderly patients with mixed chronic disease. We will use a unique, validated risk assessment index to systematically identify patients at high risk for hospitalization, ED visits, nursing home placement, and death. The study size will exceed the largest study to date for the mixed chronic disease population. We will provide a more robust analysis of key clinical outcomes and economic impacts not yet fully characterized and use these results in future studies comparing telemonitoring to care-transition programs. We will also use the results to define populations most suitable for these and similar interventions targeted to sustaining late-life independent living. This study may also provide a background for other monitoring devices.

The strengths of this study include the randomized trial approach, which will allow the groups to be randomly assigned and minimize the differences between the groups. The usual care group includes the standardized followup for patients, which is the standard of care for high-risk elderly patients in Rochester. The telemonitoring intervention group is based on cutting-edge technology for monitoring at home. The clinical group includes experienced midlevel nurse providers and RNs who oversee the management of home medical care. Patients also have a connection with their primary physician, who is informed of major clinical changes. Lastly, the group is maintained in a closed medical system of two major hospital groups in Olmsted County, with most care provided by the PCIM.

The major limitation is the lack of blinding inherent with two disparate groups of patients. This could lead to the Hawthorne Effect and lead to bias. It will not be practical to blind the providers or the patients receiving home equipment and constant monitoring at home. The limitations imposed will be mitigated despite the lack of blinding. Specifically, hospitalizations and ED visits as the primary outcome should occur regardless of arm or treatment and are not subjective measures. There is the potential for recall bias on self-reported outcomes; however, the primary outcomes should be captured by the medical record in nearly all cases.

